## Abstract

**Background:**

Amid COVID-19, and other possible future infectious disease pandemics, dentistry needs to consider modified dental examination regimens that render quality care, are cost effective, and ensure the safety of patients and dental health care personnel (DHCP). Traditional dental examinations, which number more than 300 million per year in the United States, rely on person-to-person tactile examinations, pose challenges to infection control, and consume large quantities of advanced-level personal protective equipment (PPE). Therefore, our long-term goal is to develop an innovative mobile dentistry (mDent) model that takes these issues into account. This model supplements the traditional dental practice with virtual visits, supported by mobile devices such as mobile telephones, tablets, and wireless infrastructure. The mDent model leverages the advantages of digital mobile health (mHealth) tools such as intraoral cameras to deliver virtual oral examinations, treatment planning, and interactive oral health management, on a broad population basis. Conversion of the traditional dental examinations to mDent virtual examinations builds upon (1) the reliability of teledentistry, which uses intraoral photos and live videos to make diagnostic decisions, and (2) rapid advancement in mHealth tool utilization.

**Objective:**

In this pilot project, we designed a 2-stage implementation study to assess 2 critical components of the mDent model: virtual hygiene examination (eHygiene) and patient self-taken intraoral photos (SELFIE). Our specific aims are to (1) assess the acceptance and barriers of mDent eHygiene among patients and DHCP, (2) assess the economic impact of mDent eHygiene, and (3) assess the patient’s capability to generate intraoral photos using mHealth tools (exploratory aim, SELFIE).

**Methods:**

This study will access the rich resources of the National Dental Practice-Based Research Network to recruit 12 dentists, 12 hygienists, and 144 patients from 12 practices. For aims 1 and 2, we will use role-specific questionnaires to collect quantitative data on eHygiene acceptance and economic impact. The questionnaire components include participant characteristics, the System Usability Scale, a dentist-patient communication scale, practice operation cost, and patient opportunity cost. We will further conduct a series of iterative qualitative research activities using individual interviews to further elicit feedback and suggestion for changes to the mDent eHygiene model. For aim 3, we will use mixed methods (quantitative and qualitative) to assess the patient’s capability of taking intraoral photos, by analyzing obtained photos and recorded videos.

**Results:**

The study is supported by the US National Institute of Dental and Craniofacial Research. This study received “single” institutional review board approval in August 2021. Data collection and analysis are expected to conclude by December 2021 and March 2022, respectively.

**Conclusions:**

The study results will inform the logistics of conducting virtual dental examinations and empowering patients with mHealth tools, providing better safety and preserving PPE amid the COVID-19 and possible future pandemics.

**International Registered Report Identifier (IRRID):**

PRR1-10.2196/32345

## Introduction

### Urgent Need to Transform the Dental Visit Format During Infectious Disease Outbreaks

Amid the COVID-19 pandemic, dental health care personnel (DHCP) are at great risk of contracting the SARS-CoV-2 virus due to their close physical proximity to their patients, as well as the enhanced potential for transmission of airborne viruses in the dental setting [1]. When delivering dental services, DHCP consume increased amounts and enhanced levels of personal protective equipment (PPE), equivalent to the ones used by other health care providers who provide care to COVID-19–positive patients. This PPE includes N95 respirators, goggles, gowns, head covers, and face shields. Although dentistry has practiced for years utilizing person-to-person visual-tactile examinations, now, more than ever, utilizing a wide variety of new technologies and approaches to deliver virtual dental services would have significant utility.

Aggressively converting traditional dental examinations (eg, comprehensive, limited, and hygiene recall examinations) to virtual examinations could significantly reduce the exposure risk for patients and DHCP and preserve a large volume of PPE essential to the medical and dental communities. According to the American Dental Association, as of 2019, 200,419 dentists were practicing dentistry in the United States, with 158,331 (79%) general dentists (GD) providing a range of examination visits on a daily basis [2]. GDs in the United States are conducting 564 million patient visits per year (an average of 3566 patient visits per GD) [3]. Importantly, 316 million of these 564 million patient visits (56%) are examination visits. These visits comprise 67 million (21%) new patient examinations, 40 million (13%) limited examinations, and 209 million (66%) hygiene recall examinations, which are often not linked to definite treatment delivery at the same visit. If these 316 million examinations were all (or partially) converted to virtual visits, serving as remote triage of patients’ needs, 316 million person-to-person contacts would be avoided, preserving at least 1 billion pieces of PPE per year.

In the current dental examination model (Figure 1), patients often need to have one examination visit and one hygiene visit before they get to a definite treatment visit. A dentist hygiene check visit usually includes x-rays taken by the dental hygienist and an examination completed by the dentist [4]. In a regular dental office, the dentists usually conduct hygiene examinations in between treating their chairside patients [4]. In the current COVID-19 environment and for the foreseeable future, the dentist needs to change PPE between seeing his or her chairside patient and the hygiene patient and then change to another PPE when completing the hygiene check and returning to the original chairside patient. A single hygiene check examination consumes 2 sets of PPE for the dentist alone and increases the challenge of infection control due to frequent switching of PPE and the dentist running between dental operatories. Moreover, with added time from changing PPE, extended waiting can add more frustration to that already reported by patients and dental hygienists while waiting for dentists during traditional hygiene examinations [4]. Dentistry needs changes to the dental examination regimens, especially hygiene examinations, to render quality care and ensure the safety of patients and the DHCP amid the COVID-19 outbreak.

**Figure 1 figure1:**
[figure not shown]
Current and proposed mobile dentistry (mDent) model for dental examinations. PPE: personal protective equipment.

**Rationale for Developing the mDent eHygiene Model in a Digital Era**

Our long-term goal is to develop an innovative mobile dentistry [5] (mDent) model in this digital era (illustrated in Figure 1). The mDent model refers to the practice of dentistry supported by mobile devices such as mobile telephones, tablets, personal digital assistants, and a wireless infrastructure. The mDent model combines virtual dental visits with the use of digital mobile health (mHealth) tools, such as intraoral cameras, to complete oral health screening, treatment planning, virtual hygiene examinations, and interactive oral health education, on a broad population basis. In the mDent model, before patients arrive at the dental office, they would have a virtual visit with dental office personnel to take a series of intraoral photos at home. Capable patients could do this independently by watching a photo-taking tutorial video, minimizing DHCP instruction time during a virtual visit. With the intraoral photos, the DHCP would have a preliminary idea of the patient’s oral health. The second visit would be an in-office hygiene visit conducted by the dental hygienist to complete intraoral x-ray records, a soft and hard tissue examination, and additional intraoral photos, if needed. Patients will then have a virtual dental visit, scheduled at a convenient time with the dentist, to review the findings and treatment plans before they proceed with an in-office visit to confirm the examinations and receive a definite dental treatment plan and dental treatment, as appropriate.

This mDent model will fully engage relevant stakeholders (patients, dental hygienists, and dentists) to conduct interactive oral health practices. The mDent model will also utilize a patient-driven mobile device to increase the accessibility of dental care. Moreover, in the era of COVID-19 risk, this remote virtual dental service model will lead to a well-planned dental service, better infection control, and reduced PPE consumption. As this eHygiene implementation study is a hypothesis-generating pilot study, our immediate objective is to assess the following 3 aims in the National Dental Practice-Based Research Network [6]: (1) Aim 1 is to assess the acceptance and barriers of mDent eHygiene among patients and DHCP, (2) aim 2 is to assess the economic impact of mDent eHygiene, (3) and aim 3 is to assess patients’ capability for generating intraoral photos using mHealth tools (SELFIE).

## Methods

### Overall Study Design

This study will use a 2-stage implementation study to assess the acceptance of 2 components (eHygiene and SELFIE) of the mDent eHygiene model among patients and DHCP (dentists and dental hygienists). The components are illustrated in Figure 2.

**Figure 2 figure2:**
[figure not shown]
Specific aims, study design, and outcome measures. DPC: dentist-patient communiation; SUS: System Usability Scale.

This mDent eHygiene study will use mixed methods (quantitative and qualitative) to collect outcome measures and conduct data analysis. For details, see Table 1 and the following subsections.

**Table 1 table1:** Mobile dentistry (mDent) model eHygiene objectives and outcome measures.

Aims	Outcome measurements	Brief description and justification of the outcome measures
Aim 1: assess the acceptance of and barriers to mDent eHygiene among patients and DHCP^a^	System Usability Scale (SUS); dentist-patient communication (DPC); theme of acceptance and barriers analyzed from individual qualitative interviews with the DHCP	The SUS instrument will be used to assess the acceptance of the mDent eHygiene approach. The SUS instrument [7-9] is widely adopted in business and technology industries and mHealth^b^ fields to measure and quantify the perception of product and service usability. The DPC component will be used to assesses how well the patients understand the planned treatment and the quality of the communication between the patients and dentists using eHygiene. We will use a modified questionnaire from a validated DPC questionnaire [10]. Qualitative analysis will be conducted for data from 15 individuals (5 patients, 5 dentists, 5 dental hygienists) via 30-minute virtual individual interviews. The questions during the interview will address the feedback, perceived challenges, and suggestions for improvement for the mDent eHygiene model.
Aim 2: assess the economic impact of mDent eHygiene	PPE^c^ consumption and estimated cost and eHygiene chair time per patient; eHygiene virtual visit time per patient; DHCP (dentist and dental hygienist) personnel cost related to eHygiene	Studies from other groups have shown improved cost-effectiveness using virtual dental visits [11,12]. Now, facing the PPE shortage amid the COVID-19 outbreak, the economic benefits of mDent eHygiene are promising. The magnitude, however, must be carefully evaluated, which will be assessed using the outcome measured listed in this objective via role-specific baseline and post-eHygiene questionnaires.
Aim 3: assess patients’ capability for generating intraoral photos using mHealth tools (SELFIE)	Quantity and quality of intraoral photos taken by patients, assessed by 1 dentist in the study team who will be trained for photo assessment; themes of challenges encountered by patients while taking intraoral photos themselves, by analyzing the video recordings from the SELFIE session	This objective will provide preliminary data on patient engagement with using mHealth tools, which is essential to empowering patients in the complete mDent model.

^a^DHCP: dental health care personnel.

^b^mHealth: mobile health.

^c^PPE: personal protective equipment.

### Participants and Recruitment

The mDent eHygiene study will be conducted in the Northeastern node of the National Dental Practice-Based Research Network in the United States. This mDent eHygiene study will enroll 144 patients and 24 DHCPs from 12 practices. Each practice will enroll 12 patients, 1 dentist, and 1 dental hygienist. All 144 patients and 24 DHCPs will conduct the eHygiene session (1st stage) of the study. Among enrolled patients and DHCPs, 5 patients, 5 dentists, and 5 dental hygienists will be invited for a 30-minute recorded telephone interview for a qualitative session of the eHygiene study. In addition, 12 patients will be invited to conduct a SELFIE session to evaluate their capability for taking intraoral photos by themselves, with guidance from the dental hygienist.

### Intraoral Photo Taken by a Dental Hygienist in an eHygiene Session

The dental hygienist will complete a routine hygiene visit, update x-rays, and perform a hard and soft tissue examination as part of routine clinical care. Intraoral photos of patients will be taken for research purposes following a recommended template (See Multimedia Appendix 1). Intraoral photos will be stored in Mouthwatch Teledent—a cloud-based platform for conducting Teledent visits. A series of intraoral photos will be taken by a tablet and an intraoral camera connected to a tablet. Examples of intraoral photos are shown in Figure 3.

**Figure 3 figure3:**
[figure not shown]
Patient self-taken intraoral photos: (A) front view taken on an iPhone X, on which gingival erythema and multiple white spots (de-calcification) are seen; (B) posterior photos taken with a Mouthwatch intraoral camera, where the upper panel includes photos of the lower left first molar and lower panel photos of the upper right first molar.

### Patient-Dentist Virtual Visit in the eHygiene Session

The dentist will then conduct a virtual visit with the patient lasting approximately 30 minutes at a later and suitable time within 14 days of the eHygiene intraoral photo visit, to review eHygiene findings and treatment plans.

### SELFIE Session

The self-taking of intraoral photos (SELFIE session) will be piloted by 12 (1 from each practice) of the 144 study patients who complete the eHygiene session. The intraoral camera and instructional video will be given to the patient when the patient leaves the hygiene visit. During a virtual visit with the dental hygienist, the patient will use an intraoral camera while being supervised by the dental hygienist to take a series of intraoral photos of the front and posterior teeth. This virtual visit session will be recorded.

Patients will be encouraged to think-aloud [13] about their feelings and difficulties encountered while taking photos. The think-aloud process asks users to verbalize their thoughts as they complete various tasks, allowing investigators to gain insight on participants’ thought processes in relation to the technology products.

### Study Questionnaires

Each participating patient, dentist, and dental hygienist will complete baseline and post-eHygiene role-specific questionnaires (see Multimedia Appendix 2 for the dentist questionnaire, Multimedia Appendix 3 for the hygienist questionnaire, and Multimedia Appendix 4 for the patient questionnaire) as per the study schedule. The questionnaires include the System Usability Scale (SUS), dentist-patient communication (DPC) scale, office operation, and other items detailed in Table 1.

### Qualitative Interviews

After receiving the SUS scores from all patients and DHCPs, the study team will randomly select 15 individuals (5 patients, 5 dentists, 5 hygienists) for virtual individual interviews lasting approximately 30 minutes. These 15 individuals will include those who rated above and below the average SUS score. The questions asked during the interview will address feedback and recommendations, perceived challenges, and suggestions for improvement of the mDent eHygiene model. The interviews will be standardized using an interview guide (see Multimedia Appendix 5), and interviews will be audio-recorded.

### Statistical Analysis

#### Sample Size Considerations

The sample size calculation for the primary outcome (eHygiene—SUS) was based on the primary outcome of the SUS score from patients. Various studies [7,14,15] have used the SUS scale to assess the usability of a medical service or mHealth tool and reported mean SUS scores of 47.5-81.2 (SD 9.9-21.1). Since the patients in the eHygiene study are clustered by practice, we used a cluster randomized design calculation for the sample size calculation. Assuming the difference in the SUS score between the patient-evaluated eHygiene model and other published mHealth tools has a mean of 8 and an SD of 10, a sample size of 72 patients from 12 practices (6 per practice) will achieve 90% power, at an alpha of .05. Considering the potential dropout rate, a sample size of 144 patients will satisfy the statistical power of the primary outcome.

Dentists and dental hygienists will complete the SUS for each patient when the dentist and hygienist complete an eHygiene visit, which means each dentist and hygienist will evaluate the eHygiene model 12 times. Assuming a mean difference of 30 (SD 20) between the first and last patients evaluated by the dentists and hygienists, using a paired *t* test, a sample of 7 dentists or hygienists will achieve 90% power, at an alpha of .05. Considering potential dropouts, recruiting 12 dentists and 12 dental hygienists will achieve satisfactory statistical power for this aim.

Using a cluster randomized design to calculate the sample size for the primary outcome of DPC and assuming a mean difference in the patient-evaluated DPC score between the current hygiene model and the eHygiene model of 8 (SD 10), a sample size of 48 patients from 12 practices (4 per practice) will achieve 85% power, at an alpha of .05. A sample size of 144 patients will satisfy the statistical power of the DPC outcome, while considering potential dropouts.

For the sample size calculation of the tertiary outcome (SELFIE), we expect to reach data saturation [16] (no new themes are identified) after conducting 12 individual tests. The sample size was determined based on previously published studies, where between 6 and 11 usability tests were conducted to assess technology products, for instance, smartphone app usability [17,18].

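### The 90% (SUS) and 85% (DPC) power figures come from a cluster-randomised calculation and do not describe this single-group, non-randomised study

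*Protocol article*

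**What the plan says.** All of the following is in the protocol article.

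- **Method.** Sample Size Considerations notes that patients are clustered by practice and continues: "we used a cluster randomized design calculation for the sample size calculation". The same method is named for the second outcome: "Using a cluster randomized design to calculate the sample size for the primary outcome of DPC".
- **SUS.** The assumed difference from "other published mHealth tools has a mean of 8 and an SD of 10". The result: "a sample size of 72 patients from 12 practices (6 per practice) will achieve 90% power, at an alpha of .05". The same paragraph cites published SUS SDs from 9.9 to 21.1.
- **DPC.** The assumed difference between the current hygiene model and eHygiene is also 8 with SD 10. The result: "a sample size of 48 patients from 12 practices (4 per practice) will achieve 85% power, at an alpha of .05".
- **Design.** Participants and Recruitment describes one group from 12 practices: "All 144 patients and 24 DHCPs will conduct the eHygiene session (1st stage) of the study". Study Questionnaires has the same participants answer at baseline and after eHygiene. The only random step described is the choice of interviewees (Qualitative Interviews).

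For SUS and DPC the article gives no number of arms, ICC or sidedness.

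**The concern.** Clustering by practice calls for a design effect. It does not call for a formula that compares randomised groups of practices, because this study has no such groups. The variance of a mean set against a fixed benchmark, or of a within-patient change, differs from the variance of a difference between two independent arms.

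These two calculations are the only numerical support for the number of patients, and the article calls both outcomes primary. If they belong to another design, the stated powers say nothing about what this study can detect. They also hide the input that matters most for a benchmark comparison, the SD of the SUS score, which was taken near the bottom of the cited range.

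**Working it through.** **Inputs from Sample Size Considerations:** difference 8, SD 10, alpha .05, 12 practices, m = 6 patients per practice (SUS) or m = 4 (DPC). **Assumptions:** the ICC, shown over a range, and a two-sided test unless noted.

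**1. Attempt to reproduce 90% and 85%.** For two arms of K practices each, SE = sqrt(2 × SD² × (1 + (m−1) × ICC) / (K × m)). Power comes from 8/SE, by normal approximation unless a t is named.

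*Twelve practices split 6+6, two-sided.*
- DPC at ICC 0: SE = sqrt(200/24) = 2.887 and 8/SE = 2.771, so power is 79.1% (77.4% by t on 46 df, 70.5% by t on 10 df). Any positive ICC lowers it. 85% is not reached.
- SUS at ICC 0: SE = sqrt(200/36) = 2.357 and 8/SE = 3.394, so power is 92.4%. It falls to 90% at ICC 0.019.

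*Split 6+6, one-sided.* DPC is 87.0% at ICC 0 and 85% at ICC 0.023. At ICC 0.02 SUS is 94.4%, not 90%.

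*Twelve practices per arm (24 in all), two-sided.*
- At ICC 0.2365, SUS: SE = sqrt(200 × 2.1825/72) = 2.462, power 90.1%.
- At ICC 0.2365, DPC: SE = sqrt(200 × 1.7095/48) = 2.669, power 85.0%.
- By t on 22 df at ICC 0.20: SUS 90.0%, DPC 84.2%.

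*One group of 12 practices.* The stated figures would need ICCs of 0.52 (SUS) and 0.61 (DPC) by t on 11 df, or 0.68 and 0.81 by normal approximation. By either method the two outcomes need different values.

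So, of the layouts tried, only two arms with 12 practices in each return both figures at one ICC.

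**2. Power in the actual design.** For one group, SE = sqrt(SD² × (1 + (m−1) × ICC) / (12 × m)), with t on 11 df, two-sided .05. SD 10 is taken as the SD of the SUS score and of the within-patient DPC difference.

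| ICC | SUS, 72 patients | DPC, 48 patients |
|---|---|---|
| 0.05 | >99.9% | 99.7% |
| 0.10 | 99.9% | 99.3% |
| 0.20 | 99.2% | 97.8% |

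Worked case, DPC at ICC 0.20: SE = sqrt(100 × 1.6/48) = 1.826, 8/SE = 4.382, power 97.8%. With all 144 patients (m = 12) at ICC 0.20 power is 99.8%.

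**3. Sensitivity to the SD, SUS, 144 patients.** The half-width of the 95% CI is 2.201 × SE.

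| SD | ICC | SE | Half-width | Power for 8 |
|---|---|---|---|---|
| 10 | 0.05 | 1.037 | 2.3 | >99.9% |
| 10 | 0.20 | 1.491 | 3.3 | 99.8% |
| 21.1 | 0.05 | 2.189 | 4.8 | 91% |
| 21.1 | 0.20 | 3.145 | 6.9 | 64% |

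**4. Meaning of SD 10 for DPC.** If it is the SD of single scores and baseline and follow-up are uncorrelated, the SD of the difference is 10 × sqrt(2) = 14.1. Power with 48 patients is then 91.3% at ICC 0.05 and 80.5% at ICC 0.20.

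**The case against.** The strongest reply is that the label is loose but harmless. The calculation was chosen because patients are clustered, which reads as a clustering adjustment. If DPC is measured before and after, all 12 practices contribute to both conditions, so 12 clusters per condition need not mean 24 practices. Treating the two conditions as independent ignores the pairing, which understates power when the two scores are positively correlated. Treating the SUS benchmark as a sampled group is likewise cautious. The study is presented as a pilot meant to generate hypotheses, its planned mixed models account for clustering, and a condensed article may leave the ICC to a fuller document.

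Much of this stands. The missing ICC alone would not be a finding, and at SD 10 the stated figures understate power in the actual design. What does not stand is the method as printed: it is named as cluster-randomised, twice, for a study that randomises no practice.

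Two stronger readings are tempting and are not supported:

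- *That 85% for DPC cannot be reached with 12 practices.* This holds only for a two-sided test with the practices split 6+6. The article states neither. A one-sided test in that split gives 87.0% at ICC 0, and the actual one-group design exceeds 85% up to an ICC of about 0.61 (11 df).
- *That a two-arm formula with 24 practices was used.* The numbers point that way, but the article never gives the number of arms, and the matching ICC depends on the method (about 0.24 or about 0.20).

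**Conclusion.** The point holds as a mismatch between calculation and design: the 90% and 85% do not describe this study and cannot be derived for it from the stated inputs. It does not show that the study is too small. At the article's own difference and SD, with an assumed ICC of 0.05 to 0.20, a two-sided test and 11 df, power in the actual design is about 98% or more for both outcomes, even at 72 and 48 patients. For DPC this rests on the comparison being within patients and on SD 10 being the SD of the difference.

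The practical consequence is for SUS. At the top of the cited SD range, 144 patients give about 91% power at ICC 0.05 and 64% at ICC 0.20, and the present text does not show this. The point is a moderate correction of the sample-size statement and does not stand in the way of the study.

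**What to change.** Replace the cluster-randomised calculation in Sample Size Considerations and withdraw the 90% and 85% figures.

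- **SUS:** a one-sample calculation against a named benchmark value.
- **DPC:** a within-patient calculation, stating that SD 10 is the SD of the within-patient difference, or giving that SD if it is not.
- **Both:** 12 clusters, design effect 1 + (m−1) × ICC, 11 df, the sidedness, and an assumed ICC range such as 0.05 to 0.20.
- **SUS precision:** power and expected 95% CI half-width across the cited SDs. With 144 patients the half-width is about 2.3 to 3.3 points at SD 10 and about 4.8 to 6.9 points at SD 21.1.

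The cost is rewording. Recruitment does not change. The one drawback for the sponsor is that the SUS statement becomes less favourable at the higher SDs.

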#### Analyses for Aim 1: eHygiene

We will calculate SUS scores for the eHygiene model (post-eHygiene SUS) as rated by patients, dentists, and dental hygienists. The SUS score from the patients and DHCPs between practices will be compared. A linear mixed effects model will be used to examine factors that influence the SUS score as perceived by patients, including patient factors (demographic, socioeconomic, education, profession, and experience with using a digital device and mHealth tools) and DHCP factors (demographic and dental practice experience), while considering the clustering effects within practices and providers. The eHygiene SUS score as rated by dentists and dental hygienists from treating the first patient through the last study patient will be compared to assess whether the DHCP-determined SUS score is associated with a learning curve.

We will calculate the DPC score as rated by patients, which assesses how well the patients understand the planned treatment and the quality of the communication between the patients and dentists who participate in eHygiene. We will use a linear mixed effects model to examine factors that influence the DPC score perceived by patients, including patient factors (demographic, socioeconomic, education, profession, and experience with using a digital device and mHealth tools), DHCP factors (demographic and dental practicing experience), and time spent on the eHygiene visit, while controlling for the clustering effects within practices and providers. We will run separate models for patients and DHCP.

Regarding qualitative data, the interviews will be standardized using interview guides, audio-recorded, transcribed, coded, and analyzed for thematic content. The audio recordings will be transcribed by the Temi (San Francisco, CA) transcription service and further verified by 2 trained research personnel. Transcribed data will be analyzed using MAXQDA software (VERBI GmbH, Berlin, Germany). The data will be coded by 2 trained coders with predetermined open codes using a codebook with a description of the coding tree. Thematic content will be further analyzed using categorizing and contextualizing strategies to understand the factors associated with acceptance of and barriers to eHygiene among patients and DHCPs.

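### The 90% power for the primary patient SUS outcome is for a comparison with published tools that has no stated reference value and is not among the listed analyses

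*Protocol article*

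**What the plan says.** All references are to the protocol article.

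- **Primary outcome and powered contrast** (Sample Size Considerations). The calculation "was based on the primary outcome of the SUS score from patients". The assumption is that "the difference in the SUS score between the patient-evaluated eHygiene model and other published mHealth tools has a mean of 8", with "an SD of 10, a sample size of 72 patients from 12 practices (6 per practice) will achieve 90% power, at an alpha of .05".
- **Source of a possible reference** (same section). Earlier studies of medical services or mHealth tools "reported mean SUS scores of 47.5-81.2 (SD 9.9-21.1"). No single study, pooled mean or threshold is selected.
- **Type of calculation** (same section). "we used a cluster randomized design calculation for the sample size calculation". The ICC, the number of groups and the sidedness are not given.
- **Enrolled number** (same section). "Considering the potential dropout rate, a sample size of 144 patients will satisfy the statistical power of the primary outcome". The dropout rate is not given.
- **Groups** (Participants and Recruitment). "All 144 patients and 24 DHCPs will conduct the eHygiene session (1st stage) of the study". There is no concurrent comparator.
- **SUS analyses** (Analyses for Aim 1: eHygiene). Scores are calculated for patients, dentists and hygienists. "The SUS score from the patients and DHCPs between practices will be compared". A linear mixed model then looks for factors associated with patient SUS, and the dentists' and hygienists' scores are compared from first to last patient as a learning curve.
- **Table 1** says that SUS measures acceptance and gives no benchmark.

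**The concern.** A power statement belongs to a specific test. Here it belongs to a difference between eHygiene and something published, but the analysis section contains no such difference. A comparison between practices and a regression on patient and provider factors answer other questions, and the 8-point, 90% figure says nothing about the power of either.

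Two things can follow if the plan is carried out as written. The powered comparison may never be made, and the sample-size justification then supports nothing that is reported. Or it may be made at the reporting stage against a reference chosen once the eHygiene mean is known. The cited means lie far enough apart for that choice to decide whether eHygiene looks better or worse than what has been published.

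**Working it through.** **1. The plan's own figure.** Stated: difference 8, SD 10, 72 patients in 12 practices of 6, alpha .05, power 90%. The ICC, number of groups and sidedness are not stated, so I assume two-sided .05 and try the possible layouts. The design effect is DE = 1 + (m − 1) × ICC with m = 6.

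- *Two groups of 6 practices (36 v 36).* SE = 10 × √(2 × DE/36). At ICC 0, SE = 2.357 and 8/2.357 = 3.394, giving power 92.4% (normal) or 91.7% (t, 70 df). At ICC 0.02 the power is 89.9% (normal).
- *Two groups of 12 practices (72 v 72).* At ICC 0.20, DE = 2 and SE = 10 × √(2 × 2/72) = 2.357, giving power 90.0% (t, 22 df).
- *One group of 72 against a fixed value.* SE = 10 × √(DE/72). At ICC 0.20, SE = 1.667 and 8/1.667 = 4.8, giving power 99.2% (t, 11 df); it is higher at smaller ICCs. Power falls to 90% only at an ICC of about 0.52 (t, 11 df) or 0.68 (normal).

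So 90% is matched by two-group layouts with a modest assumed ICC, and by the one-group layout only at a very high ICC. With the ICC unstated, the figure can be neither uniquely reproduced nor refuted. The pattern suggests, without proving it, that the calculation was not set up for the one-group comparison that this study could make.

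**2. Does any listed analysis make the powered contrast?**

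| Listed SUS analysis | Compares patient SUS with a published value? |
|---|---|
| Calculate post-eHygiene scores | No |
| Compare between practices | No |
| Mixed model for associated factors | No |
| First-to-last-patient change in dentists and hygienists | No |

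The article does carry another powered contrast through: the first-to-last change in dentists and hygienists is powered in one section and analysed in the next. The patient SUS contrast has no such counterpart.

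**3. How much the choice of reference can matter.** Span of cited means: 81.2 − 47.5 = 33.7 points, and 33.7/8 = 4.2 times the assumed difference. Take an illustrative patient mean of 65 (not a figure from the article):

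- against 47.5: 65 − 47.5 = +17.5
- against 81.2: 65 − 81.2 = −16.2

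The 95% CI half-width with 144 patients (12 practices of 12) and 12 − 1 = 11 df is t(0.975, 11) × SD × √((1 + 11 × ICC)/144), with t = 2.201. The SDs are the planning value and the top of the cited range; the ICCs are my assumptions.

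| SD | ICC 0.05 | ICC 0.20 |
|---|---|---|
| 10 | 2.3 | 3.3 |
| 21.1 | 4.8 | 6.9 |

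Both differences exceed the widest half-width, so each would be significant, in opposite directions.

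**4. Power of the one-group test.** Cluster-adjusted one-sample t test, 11 df, two-sided .05, difference 8, assumed ICCs:

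| SD | ICC | 72 patients | 144 patients |
|---|---|---|---|
| 10 | 0.20 | 99% | above 99% |
| 21.1 | 0.02 | 80% | 96% |
| 21.1 | 0.05 | 75% | 91% |
| 21.1 | 0.20 | 55% | 64% |

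**The case against.** The strongest reply is that Aim 1 is to assess acceptance and barriers, in what the article itself calls a hypothesis-generating pilot. The 8-point difference is introduced as a planning assumption, not as a hypothesis or an acceptance threshold. Patient SUS will be calculated and modelled with allowance for clustering, and acceptance is also judged by dentist-patient communication, provider-rated SUS and interviews. All of this stands. A reader might infer that the primary question has no valid test, or that eHygiene will be declared a success or failure on a benchmark of choice. The article supports neither: it contains no success rule, and mean SUS remains estimable.

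The span of 33.7 points also overstates the choice to some degree. The cited studies cover medical services as well as mHealth tools, while the stated comparator is mHealth tools only, so the span is an upper bound. Which of the cited studies would qualify cannot be seen.

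A reader might also infer that the 90% is wrong or the study too small. With the ICC unstated, the first cannot be shown. On the plan's own SD of 10 the second is untrue for a one-group test at ICC 0 to 0.20.

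Finally, a reference value and test could sit in a full protocol or SAP that is not shown. That limits the finding to this article. It does not remove the mismatch between two of its adjoining sections, where one claims power for a comparison and the other lists the analyses without it.

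**Conclusion.** The concern holds in this form: the power stated for the primary outcome attaches to a comparison for which the article gives no reference value and lists no analysis, in a study with one group. The possible effect is a reversal of direction, shown above for a mean of 65 against the two ends of the cited range. That illustration rests on an invented mean, assumed ICCs of 0.05 to 0.20, and the assumption that both ends of the range are eligible references.

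The matter should be fixed, but it does not undermine the study. No data collection is affected, the SUS mean can be reported with a valid interval, and no planned decision depends on the missing comparison.

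**What to change.** Align Sample Size Considerations with Analyses for Aim 1 in one of two ways.

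(a) **Keep the comparison.** Before SUS data are read, name one numeric SUS reference and its source. Add to the Aim 1 analyses a cluster-adjusted one-sample comparison of mean patient SUS with that value: a covariate-free mixed model with a practice random intercept and a 95% CI on 11 df. Say that the reference is treated as fixed, and that its own sampling error and any difference in population are therefore ignored. Restate the power for this one-group test with a stated ICC and SD.

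(b) **Declare estimation primary.** Report mean patient SUS with a clustered 95% CI. Replace the 90% power claim with the expected half-width, which for 144 patients and an assumed ICC of 0.05 is about 2.3 points at SD 10 and 4.8 at SD 21.1. Label any comparison with published tools as descriptive.

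Option (b) is close to what the analysis section already describes and suits a hypothesis-generating pilot. Either costs about one paragraph of text and needs no new data and no change to recruitment.
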